#### **Visit 4-14\*, week 4-40 (-60), duration 2 hours/visit: up-dosing OIT peanut**

The patient comes for up-dosing according to Table 3 with a predefined increase of peanut protein every 4-6th week up to 285 mg, maintenance dose (= 1.3 peanut = 3 pieces of Bamba), or the dose reached by the child after 60 weeks of up-dosing.

A physical examination is conducted, and a standardized questionnaire is filled in by the physician regarding physical status before the start of up-dosing. The diary is collected and reviewed. Only if the child has fully tolerated the previous dose and has not had any allergic side effects the last week, up-dosing is performed. The up-dosing is performed under the supervision of a research nurse and a physician at the study center. The child is observed for 90 minutes after the dose. The families/patients are informed about co-factors for allergic reactions e.g. high physical activity 3 hours after the dose intake. The up-dosing phase is ongoing for 40-60 weeks. If the patient becomes ill or cannot come to the study center after 6 weeks, the same dose is maintained until a new visit for up-dosing is made. If allergic reactions occur, the dose is changed according to Table 4. If for some reason (such as acute illness) the patient fails to take his/her OIT, the dose will change according to Table 5.

Between all the visits the families can contact the study nurse by telephone or mail if needed. If a moderate/severe allergic reaction/adverse event occurs during on-call time, the families are referred to one of Stockholm's children's emergency wards which will be informed about the study. Material for fecal samples is provided at visit 14.

#### **Visit 15, approximately 1 year after starting OIT, duration 6 hours: peanut challenge 2**

One year (approximately) after OIT starts the second peanut challenge is made at the study center according to the same schedule as in the baseline challenge, however the start will be at a higher dose (Table 2b). Sampling of blood (20 ml) and fecal sample is repeated (Table 1). Questions about quality of life will be answered by the parents.

#### **Visit 16-22\*, year 2-3, duration 30 min/visit: OIT maintenance dose**

Continued treatment with the same maintenance dose daily (285 mg peanut protein) for further 2 years, a total of treatment time, 3 years. Follow-up visits for clinical control during the 2 years maintenance phase take place every third months. At the visits, the child should eat his/her maintenance dose and stay for 30 minutes. The study staff goes through the diary. Between the visits the families can contact the study nurse by telephone or mail if needed. If a moderate/severe allergic reaction/adverse event occurs during on-call time, the families are referred to one of Stockholm's children's emergency wards which will be informed about the study.

### **Visit 23\*, after 3 years of OIT treatment, duration 6 hours: peanut challenge 3**

After totally 3 years of OIT treatment a peanut challenge is performed, up to 5 g of peanut protein (Table 2b). If the challenge is negative at dose step 2, cumulative dose of 750 mg of peanut protein, without dose-limiting symptoms, OIT is discontinued, and peanuts should strictly be avoided for 4 weeks. Sampling is repeated, blood sample, 20 ml and fecal sample (Table 1). Questions about quality of life will be answered by the parents.

### **Visit 24\*, after 4 weeks of strict peanut avoidance, duration 6 hours: peanut challenge 4**

Peanut challenge is performed after 4 weeks without any peanuts to control sustained unresponsiveness and maintained tolerance. Sampling of blood (20 ml) and fecal sample is repeated (Table 1). Children who pass the 4th peanut challenge are considered peanut tolerant. Families will be advised to continue giving peanuts regularly e.g. every day to 3 times a week, but families will decide how to continue.

\* More visits may occur (due to illness, not tolerating the dose etc.).

## **Group 2: Peanut allergic children with peanut avoidance**

### **Visit 3, after 1 year, duration 6 hours: peanut challenge 2**

One year after the first peanut challenge a second peanut challenge is performed at the study center according to the same schedule as in the baseline challenge (Table 2a). Sampling of blood (20 ml) and fecal sample is repeated, Table 1. Before the challenge the medical status of the child will be checked and information from the parents if there have been any allergic reactions to peanuts last year. Questions about quality of life will be answered by the parents.

### **Visit 4, after 3 years, duration 6 hours: peanut challenge 3**

Three years after the first peanut challenge a third peanut challenge is performed at the study center according to the same schedule as in the baseline challenge (Table 2a). Sampling of blood (20 ml) and fecal sample is repeated, Table 1. Before the challenge the medical status of the child will be checked and information from the parents if there have been any allergic reactions to peanuts last year. Questions about quality of life will be answered by the parents.

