#### Inclusion criteria

- Children 12-47 months at inclusion
- Positive baseline challenge at a maximum of the 250 mg peanut protein-dose and with at least one objective symptom at peanut challenge or positive peanut challenge performed in the clinic in a similar way within 1 year from study start
- IgE-ab to peanut and/or Ara h 2  $\geq 0.1$  kUA/l, analyzed within 12 months from start of study
- Written consent for participation in the study from all caregivers

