## Intervention substance

For the lower peanut OIT doses we will for practical reasons use peanut flour (peanøttmel, 50% protein content, Sukrin, Oslo, Norway) mixed with oat flour (Havremjöl glutenfritt, Urtekram, Midsona AB, Jylland, Denmark). For higher OIT doses (from 32 mg peanut protein) and the maintenance dose we will use “BAMBA” - a peanut-coated corn puff that dissolves in the mouth and contains 50% peanut and used in the LEAP study (Osem Food Industries, Shohan, Israel).

## Visits - groups 1 and 2

**Visit 1, screening visit, duration 1 hour:** the child and parents come to the Research Center at Sachs' Children and Youth Hospital for an information and screening visit. Written consent from both parents / legal guardians is mandatory to participate in the study. At the visit the families will be informed about the study design, follow-up schedule and adverse events that

may arise. A medical history on previous allergic reactions to peanuts and other background factors is collected. If necessary, the study physician will also review the medical records. Materials for fecal samples are provided.

**Visit 2, baseline challenge, duration 6 hours:** all children with a suspected peanut allergy, groups 1 and 2, undergo an open peanut challenge with peanut flour using (Table 2a). Before the start of the challenge, the child is examined by the physician according to a pre-set form. Only children free of infections and ongoing allergic symptoms may undergo challenge. For safety reasons, all children will receive a peripheral venous catheter after local anesthesia (EMLA). From the peripheral venous catheters, blood samples for immunoglobulins, blood status and immunological markers (20 ml) will be drawn (Table 1). Questions about quality of life will be answered by the parents. Observation time will be 2 hours after the last dose. If the child has undergone an equivalent challenge in the clinic within 1 year, no new challenge needs to be done.

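### Control challenges are timed from a first challenge that may predate entry by up to a year, while the OIT group's are timed from OIT start, so some controls are assessed early

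*Protocol*

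**What the plan says.** The two randomised groups run on different clocks.

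- **Group 2.** Visit 3: "One year after the first peanut challenge a second peanut challenge is performed at the study center". Visit 4: "Three years after the first peanut challenge a third peanut challenge is performed at the study center". Visit 4 is this group's last challenge.
- **What can count as the first challenge.** The inclusion criteria accept a "positive peanut challenge performed in the clinic in a similar way within 1 year from study start". The Visit 2 description adds: "If the child has undergone an equivalent challenge in the clinic within 1 year, no new challenge needs to be done".
- **Group 1.** Visit 15: "One year (approximately) after OIT starts the second peanut challenge is made at the study center". Visit 23: "After totally 3 years of OIT treatment a peanut challenge is performed". Children without dose-limiting symptoms at dose step 2 of that challenge stop OIT and go on to Visit 24: "Peanut challenge is performed after 4 weeks without any peanuts to control sustained unresponsiveness and maintained tolerance".

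The Outcomes paragraph applies the primary outcome to groups 1 and 2. Table 1 dates its year-1 and year-3 columns from OIT start for every group listed, including Group 2, which has no such date. Nothing in the protocol moves a Group 2 child's clock to randomisation or entry when a clinic challenge is used.

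**The concern.** The age of a clinic challenge shortens follow-up after entry in one arm only. In Group 1 it has no effect on the schedule, because the clock starts with treatment. In Group 2 it is subtracted from the follow-up. Randomisation can balance the number of children who enter on older challenges, but it cannot cancel a rule that treats them differently once allocated.

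The power calculation allows 10% tolerance in untreated children. If that tolerance accrues with time, testing some controls earlier lowers the control rate and moves the primary comparison towards OIT. The secondary comparisons are exposed as well. For a control with an old qualifying challenge, the year-1 blood, stool and quality-of-life assessments fall close to the baseline ones, so a change over one year is not what is measured.

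**Working it through.** **Plan's own figure.** The protocol gives no interval between the arms' assessments to reproduce. Its sample sizes (30 + 15 for 50% against 10%, and 12 + 6 for 75% against 10%) do reproduce with a two-sided 5% test, pooled variance, no continuity correction and 80% power. They do not depend on this point.

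**Inputs.** L = age in months of the clinic challenge at entry, 0 to 12 (inclusion criteria; Visit 2). g = months from entry to OIT start, not stated; set to 0 below. Off-treatment period = 4 weeks = 28/30.44 = 0.92 month (Visit 24). Entry is taken as the date of randomisation.

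**Timing, in months after entry.** Group 2 year-1 challenge: 12 − L. Group 2 year-3 challenge: 36 − L. Group 1 Visit 23: 36 + g. Group 1 Visit 24: 36 + g + 0.92. The gap to Visit 23 is L + g, and the gap to Visit 24 is L + g + 0.92.

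| L | Group 2 year-1 | Group 2 year-3 | Gap to Visit 23 | Gap to Visit 24 |
|---|---|---|---|---|
| 0 | 12 | 36 | 0 | 0.92 |
| 3 | 9 | 33 | 3 | 3.92 |
| 6 | 6 | 30 | 6 | 6.92 |
| 9 | 3 | 27 | 9 | 9.92 |
| 12 | 0 | 24 | 12 | 12.92 |

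Any delay g adds to both gaps. At L = 12 the year-1 assessment falls due at entry.

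**Effect on natural tolerance (illustration).** Assume a constant rate, counted from the challenge at which the child was last shown to be allergic. With p the 36-month proportion, F(t) = 1 − (1 − p)^(t/36). A control is always tested at t = 36 on this clock, whatever L is. A Group 1 child with the same L, counting natural tolerance only, is tested at about t = 36 + L + 1 at Visit 24.

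- p = 0.10: control 10.0%. Group 1 counterpart at L = 0: 1 − 0.9^(37/36) = 10.3%. At L = 6: 1 − 0.9^(43/36) = 11.8%. At L = 12: 1 − 0.9^(49/36) = 13.4%.
- p = 0.30: control 30.0%. Counterpart at L = 0: 1 − 0.7^(37/36) = 30.7%. At L = 6: 1 − 0.7^(43/36) = 34.7%. At L = 12: 1 − 0.7^(49/36) = 38.5%.

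The worst-case differences are 13.4 − 10.0 = 3.4 points and 38.5 − 30.0 = 8.5 points. Of these, 0.3 and 0.7 points come from the 4-week period, which is present even at L = 0.

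**In children.** If all 25 controls were at L = 12, this is 25 × 0.034 = 0.85 of a child, or 25 × 0.085 = 2.1 children.

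**After re-anchoring.** With both arms counted from randomisation, L drops out. The gap to Visit 23 is g. If the control challenge is set at 3 years plus 4 weeks, only g remains against Visit 24.

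**The case against.** The phrase may have been written with the ordinary flow in mind: a positive challenge at Visit 2, consent, randomisation. In that flow the first challenge and entry nearly coincide. The visit headings speak simply of 1 and 3 years, and Table 1 puts Groups 1 and 2 in shared columns. Its OIT-start label also covers Group 3, whose second visit is counted from inclusion, so the label looks like shorthand for a common study clock. A team would hardly collect year-1 samples at entry.

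This makes the intention plausible, but it does not supply a rule. Where the clinic challenge replaces Visit 2's, no baseline challenge exists at the study centre, so reading the phrase as the first challenge there leaves the later visits without an origin. The numbering of second and third challenges also fits the clinic challenge being the first.

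The objection on size stands. Two stronger readings are tempting:

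- A reader might infer that controls are in general tested 13 months early. That is a ceiling. It needs a clinic challenge almost exactly 12 months old, and about 1 month of it belongs to the 4-week off-treatment design. Nor does every Group 1 child wait that extra month: those who fail at Visit 23 are not described as going on to Visit 24.
- A reader might start the tolerance clock at randomisation and infer that the control rate drops to 6.8% at 24 months (or 21.2% with 30% assumed). These children were last shown to be allergic at the earlier clinic challenge, so on the same model they have had 36 months, and the control rate stays at 10% or 30%.

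**Conclusion.** The point holds at moderate severity. As written, the timing rule shortens follow-up after entry in controls only, by the age of the clinic challenge (up to 12 months). About 1 month is added in the comparison with Group 1 children who reach Visit 24, plus any delay before OIT starts. The direction is towards OIT.

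The average size cannot be computed, because the share of children entering on a clinic challenge and the ages of those challenges are not stated. The worst-case figures of 3.4 and 8.5 points apply only to children at L = 12. They rest on three assumptions: a constant tolerance rate, a clock that starts at the qualifying challenge, and a 3-year rate of 10% or 30%. The protocol does not tie its 10% to 3 years, and the 30% is an assumed upper value. If half the controls had L = 6 and half L = 0 (an assumption), the 10% case gives 0.5 × 1.8 + 0.5 × 0.3 = about 1 point, or roughly a quarter of a child among 25.

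Against a planned difference of 50 − 10 = 40 points, this would not by itself decide the trial. It is nevertheless a one-directional bias in the primary comparison, and follow-up time not observed cannot be recovered in the analysis. For a child with a large L, the year-1 immunology and quality-of-life data lose most of their meaning.

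**What to change.** - In Group 2, Visits 3 and 4, count the year-1 and year-3 assessments from the date of randomisation, whether the qualifying challenge was done at Visit 2 or in the clinic.
- Place Group 2's final challenge in the same window as Group 1's Visit 24, so that the primary outcome is assessed at comparable times in both arms.
- In Group 1, record the interval from randomisation to OIT start. For every child in both groups, record the date of the qualifying challenge, so that the remaining difference can be reported.
- Relabel Table 1's year-1 and year-3 columns to the common date.

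The cost is one sentence in each of two visit descriptions, a table header and two dates in the database. No visits are added.

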## Oral immunotherapy for young children with peanut allergy – Small Children OIT (SmaChO)

### Materials and Methods

#### Study population

Children aged 12-47 months with IgE-ab to peanut extract and/or Ara h 2  $>0.1$  kUA/L are identified via the Karolinska University Laboratory in Stockholm. All eligible families will receive an information letter about the study. Interested families with children with possible peanut allergy (groups 1 and 2) will be able to contact the study team. If we do not receive enough potential participants, renewed contact is made by telephone to investigate if there is an interest in participating in the study. Children/families can also be recruited on the visits to allergy clinics or be referred to by colleagues from other healthcare facilities in Stockholm. Children without allergies will be asked to participate as a healthy control group (group 3).

Children, 12-47 months at inclusion, (n=75 with peanut allergy; at least one objective symptom at a peanut challenge and IgE-ab to peanut/Ara h 2  $>0.1$  kUA/l). Families who want their child to have peanut OIT will be randomized 2:1 to either group 1 or 2.

**Group 1;** 50 children, randomized to treatment: peanut OIT with slow up-dosing every 4-6 weeks (in total 40-60 weeks up-dosing period), until a maintenance dose of 285 mg peanut protein, total treatment time 3 years.

**Group 2;** 25 children, randomized to continue with peanut avoidance. This group will be offered OIT after the study is finished if there is a clinical available OIT to peanut at that time point.

**Group 3;** healthy controls: 20 children 12-47 months without allergic disease.

**Outcomes:** The primary outcome is defined as sustained unresponsiveness to 750 mg peanut protein (cumulative dose) at an open oral peanut challenge 4 weeks after 3 years of OIT was stopped (group 1 and 2). Secondary outcomes are adverse events among peanut allergic children with/without OIT treatment (group 1 and 2), and changes in quality-of-life parameters and immunological markers (group, 1, 2, 3).

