### **Group 1, Peanut Allergic Children Undergoing OIT Peanut, Slow Up-dosing**

#### **Visit 3, week 0, duration 6 hours: start immunotherapy:**

Clinical examination of the child is performed and noted in a standardized form. The peanut OIT starts with 1/4 of the dose (at least 3 mg of peanut protein) that gave the first reaction at baseline challenge, e.g. if reaction occurred at 100 mg of peanut (25 mg of peanut protein), the start dose will be 6 mg. Four doses will be given at the study center with 20-30 min intervals with 0.8, 1.5, 3 and 6 mg of peanut protein. The patient will be observed for 90 minutes after the last dose. If the last dose of peanut protein is tolerated (in the example 6 mg), this dose will be ingested daily at home for 4 weeks (Table 3) in the form of peanut flour mixed with oat flour for the lower doses and Bamba (a peanut-coated corn puff that dissolves in the mouth and contains about 50% peanut protein) from dose 32 mg peanut protein. The study participants are provided from the study center with peanuts in the appropriate form and quantity.

The families receive information on how to fill in a diary at home, which records daily intake of peanut, adverse events (all symptoms that occur during the study period regardless of whether they can be associated with peanut intake) and drugs that the child receives during the study period. The diary is filled in by the parents between the visits and taken to all visits where the study physician goes through the diary together with a parent/the parents.

All study participants will get an "emergency kit", adrenaline autoinjector for intramuscular injection, antihistamine, and b2-agonist for inhalation if the participant has a known asthma. Oral corticosteroids will be provided if the family lives far away from hospital; corticosteroids take 2-3 hours before effect. The parents receive written instruction and a practical demonstration on how/when to use the medications. They will also get instructions on when to contact the study team and/or make an acute hospital visit.

All study participants are instructed to strictly avoid any other intake of peanuts, apart from the OIT doses.

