### Data Collection

Each individual receives a unique code for identification. The results of the challenges and completed diaries signed consent forms, that are available in paper form are saved in binders stored at the Children's Research Center, Södersjukhuset in locked space until they are entered into the database. All data will be entered into a secure database (RedCap) with only code numbers as identification. In addition, web-based questionnaires and diaries are filled by the guardians directly into the database under code numbers. Analyzed data on blood and feces samples are entered into the database. A code key connecting the individual information and code numbers will be stored, locked in at the Research Center, Södersjukhuset's server, accessible only to the principal investigator, research physician and research nurse. The material will be saved for about 10 years.

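### Adverse events are a secondary outcome in both randomised groups, but the protocol describes an all-symptom diary for Group 1 and only recall of peanut reactions at years 1 and 3 for Group 2

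*Protocol*

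**What the plan says.** The Outcomes paragraph under Study population reads: "Secondary outcomes are adverse events among peanut allergic children with/without OIT treatment (group 1 and 2". Both randomised groups are named.

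For Group 1, the visit that starts immunotherapy (Visit 3, week 0) introduces a home diary of daily peanut intake, drugs received and "adverse events (all symptoms that occur during the study period regardless of whether they can be associated with peanut intake". It also says: "The diary is filled in by the parents between the visits and taken to all visits". The up-dosing section (Visits 4-14, every 4-6 weeks) adds: "The diary is collected and reviewed". For maintenance (Visits 16-22, every third month) the text is: "The study staff goes through the diary".

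For Group 2, there are two visits after baseline, at 1 year and 3 years. At each, the child's medical status is checked before the challenge and the staff obtain "information from the parents if there have been any allergic reactions to peanuts last year". The sentence is the same at both visits. The second visit is timed as follows: "Three years after the first peanut challenge a third peanut challenge is performed at the study center". The Group 2 sections mention no diary and no contact between visits.

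The Data Collection section says that "web-based questionnaires and diaries are filled by the guardians directly into the database under code numbers", without naming a group.

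**The concern.** A between-group comparison of adverse events needs the same events to be looked for, in the same way and over the same time, in both groups. As described, the groups differ in scope (all symptoms against peanut reactions), in method and intensity (a running diary with frequent review against recall at two visits) and possibly in the period covered.

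Two things are at stake. Children aged 12-47 months at inclusion will have symptoms unrelated to peanut. Group 1's diary counts these, and without a matching record in Group 2 there is no background rate against which to read them. Peanut reactions during avoidance are also the events that long recall is likely to miss. Both effects push towards more recorded events in Group 1. An analysis plan cannot repair this afterwards, because it cannot recover events that were never collected.

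**Working it through.** **The plan's own figures.** The protocol gives no figure for the adverse-event outcome. Its only calculation is the sample size for the primary outcome: 10% against 50%, 80% power, 5% level, 2:1 allocation. With r = 2 and pooled proportion (0.10 + 2 × 0.50)/3 = 0.367, the two-sided formula without continuity correction gives

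n₂ = [1.96 √(1.5 × 0.367 × 0.633) + 0.842 √(0.09 + 0.25/2)]² / 0.40² = (1.157 + 0.390)² / 0.16 ≈ 15,

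hence 15 + 30, as stated. The same formula for 10% against 75% gives 6 + 12, also as stated. Neither depends on how adverse events are collected.

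**Collection side by side.**

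| | Group 1 | Group 2 |
|---|---|---|
| Events | All symptoms, linked to peanut or not; drugs | Allergic reactions to peanut |
| Method | Parent diary, reviewed by study staff | Parental recall; status check before challenge |
| Planned visits after baseline or OIT start | Visits 4-24, that is 21 | Visits 3 and 4, that is 2 |
| Months covered, literal reading | 0-36 | 0-12 and 24-36 |
| Months covered, if the question means since the last visit | 0-36 | 0-36, the last 24 by a single recall |

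**Period covered.** Under the literal reading, Group 2 is asked about 12 + 12 = 24 of 36 months (67%). Months 12-24 (33%) fall between the two questions.

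**Effect on peanut reactions, literal reading.** Assume the same true rate λ per child-year in both groups, constant over time, with perfect recall. These are assumptions; the documents give no event rates.

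- Rates over a 36-month denominator: Group 1 records λ, Group 2 records λ × 24/36. The apparent ratio is 36/24 = 1.5.
- Group 2 divided by the 24 months actually asked about: the ratio is 1.0.
- Proportion with at least one recorded event, 1 − exp(−3λ) against 1 − exp(−2λ): 26% against 18% at λ = 0.1, 45% against 33% at λ = 0.2, 78% against 63% at λ = 0.5.

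**Effect of scope.** Suppose a share s of all adverse events are peanut reactions, true rates are equal, and nothing else reaches the Group 2 record. The apparent ratio for all adverse events is then 1/s once the period is fully covered, and 1.5/s under the literal reading with a 36-month denominator. For assumed s of 0.5, 0.25 and 0.1, 1/s is 2, 4 and 10, and 1.5/s is 3, 6 and 15. The documents give no s and do not say that nothing else is recorded in Group 2. The range shows only that closing the year-2 gap does not by itself make the groups comparable.

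**The case against.** Several stronger readings are tempting, and the documents do not support them.

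- *Year 2 is never recorded in Group 2.* The year-3 sentence repeats the year-1 sentence word for word. At year 1 the phrase does mean the time since the previous challenge, so at year 3 it may simply have been carried over. The gap is what the words say, but it may not be what was intended. The ambiguity still needs correcting, and the looser meaning leaves the differences in scope, method and recall length.
- *The rate ratio is inflated 1.5-fold.* No shown text specifies a rate ratio, a test or a 36-month denominator for this outcome, and with a 24-month denominator the inflation for peanut reactions disappears. The figure is conditional.
- *Non-peanut events have no capture at all in Group 2.* This argues from silence. The Data Collection sentence on diaries names no group, and medical status is checked at both visits. Group 2 challenges follow the baseline schedule, and at the baseline challenge the reacting dose is noted and symptoms are graded. What can be said is that the text describes no diary or general event history for Group 2. The status check concerns the child's condition before the challenge, and the diary is introduced only under Group 1.
- *Any difference would reflect collection rather than treatment.* Reactions to daily OIT doses can occur only in Group 1, so part of any excess is a real consequence of treatment. The diary also serves up-dosing decisions that Group 2 does not have.

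It is also fair to say that the bias runs against OIT and does not hide its harms. That limits the seriousness of the point but does not make the comparison valid.

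**Conclusion.** The point holds as a defect in data collection for a secondary outcome. As described, adverse events are ascertained differently in the two groups in scope, method and intensity, and, on a literal reading, in the period covered (24 of 36 months in Group 2). A between-group comparison would be biased towards more recorded events in Group 1. The documents do not fix the size of that bias. The factor of 1.5 applies to peanut reactions only, and only under the four conditions of literal reading, constant rate, perfect recall and a 36-month denominator.

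The conclusion rests on the protocol text available. A statement elsewhere that Group 2 keeps the same diary would remove most of it. Severity is should-fix: the primary outcome and the sample size are unaffected.

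**What to change.** 1. In the Group 2 sections for the 1-year and 3-year visits, replace *last year* with *since the last study visit*. Ask about all adverse events and drugs, using the Group 1 definitions.
2. Preferably, let Group 2 families report events between visits through the web database described under Data Collection, and state there which groups complete which diary. This shortens the two-year recall that rewording alone would leave.
3. Restrict the between-group comparison to events ascertained the same way in both groups, for example anaphylaxis, adrenaline use and emergency visits. Report Group 1 dosing-diary symptoms descriptively. The restriction is needed even with step 2, because occasional reporting in Group 2 would still be less intensive than the Group 1 diary.

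The cost is a few sentences of protocol text, a longer question at two visits and, if step 2 is adopted, what should be a small reporting burden for 25 families. The database already exists.
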